### Study outcomes

2.5

#### Primary outcome

2.5.1

The primary outcome is the change in the NSSI level score from baseline to post-intervention. The frequency and resulting harm of NSSI are assessed using the Adolescents Self-Harm Scale (ASHS), a 19-item self-report questionnaire (28). An ASHS total score greater than 0 indicates the presence of NSSI behavior. The NSSI level score is calculated by multiplying its frequency score by its harm score. A higher total score indicates greater NSSI severity (Cronbach’s α=0.93-0.97) (29).

#### Secondary outcomes

2.5.2

Depressive symptom: The 17-item Hamilton Depression Rating Scale (HAMD-17) is the most widely used clinical instrument for assessing depressive symptom severity (30). It consists of 17 items, with a total score ranging from 0 to 52. A higher total score indicates greater severity of depressive symptoms (Cronbach’s α=0.92) (31).Alexithymia: The Toronto Alexithymia Scale (TAS-20) is used to assess alexithymia in individuals (32). It comprises three factors: difficulty identifying feelings, difficulty describing feelings, and externally oriented thinking. The scale consists of 20 items, with a total score ranging from 20 to 100. A higher score indicates greater severity of alexithymia (Cronbach’s α=0.82) (33).General Self-Efficacy: The General Self-Efficacy Scale (GSES) is used to measure general self-efficacy, assessing an individual’s positive self-belief in coping with various life challenges (34). It is a self-report instrument. The Chinese version of the scale has demonstrated good reliability and validity in Chinese adolescent populations. It consists of 10 items, with a total score ranging from 10 to 40. A higher score indicates a higher level of self-efficacy (Cronbach’s α = 0.86) (35).Sleep: The Pittsburgh Sleep Quality Index (PSQI) is used to assess an individual’s recent sleep quality (36). It comprises 19 self-rated items and 5 bed-partner-rated items, of which the 19th self-rated item and all 5 bed-partner-rated items are not scored. The total score ranges from 0 to 21. The first 18 items form seven components: subjective sleep quality, sleep latency, sleep duration, habitual sleep efficiency, sleep disturbances, use of sleeping medication, and daytime dysfunction. A higher total PSQI score indicates poorer sleep quality (Cronbach’s α =0.81) (37).qLoneliness: The UCLA Loneliness Scale (UCLA-LS) is used to assess an individual’s level of loneliness (38). It consists of 20 items, with a total score ranging from 20 to 80. A higher total score indicates a greater sense of loneliness (Cronbach’s α = 0.90) (39).

### Data collection and quality control

2.6

At the baseline assessment(T_0_), the researcher will collect participants demographic data (age, gender, residence, only-child status, family structure, and family economic status, etc.) and Disease-related information (age of onset, duration of illness, and family history of mental illness, etc.). All outcome measures (primary and secondary outcomes) will be assessed at both baseline (T_0_) and immediately post-intervention (T_1_). These measures comprise the ASHS, HAMD-17, TAS-20, GSES, PSQI, and UCLA-LS.

The following quality control measures will be implemented to ensure standardization and accuracy in data collection and entry:

All researchers will receive systematic training to ensure the standardization and consistency of scale administration and data collection.Assessments for each participant at all study time points will be conducted by the same researcher member whenever possible.This trial employs well-established scales and questionnaires with good reliability and validity.Researchers will administer the scales and questionnaires to participants in a quiet, indoor setting using a one-on-one format. Standardized instructions will be provided to explain the scales and questionnaires, ensuring participants correctly and fully understand the items. Upon completion, the scales and questionnaires will be collected immediately. Researchers will then check for completeness. Any missing items will be clarified with the participant and promptly completed.After collection, all scales and questionnaires will undergo initial screening and coding. Data will then be entered into an electronic database using a double-data entry method by two independent personnel. Any discrepancies between the two entries will be adjudicated by a third researcher through verification against the original paper records.

For participants who discontinue the intervention early, every effort will be made to collect all primary and secondary outcome measures at the originally scheduled time point, T_1_. If a participant withdraws consent for further participation but agrees to data use, data collected up to the point of withdrawal will be retained and included in the ITT analysis. Reasons for discontinuation will be documented. In the ITT analysis, missing outcome data from early withdrawals will be handled using multiple imputation as the primary method, with the last observation carried forward used in sensitivity analyses.

### Data management and monitoring

2.7

All information generated during the trial will be accurately, promptly, and completely recorded in the case report forms (CRF). All data for this study will be de-identified and kept strictly confidential, with access limited to authorized personnel. If a participant withdraws consent for data use, their personal data will be completely deleted. All other data will be stored in anonymized form for at least five years after the publication of results.

Given the short intervention duration, modest sample size, and the low-risk nature of this behavioral intervention, an independent external Data Monitoring Committee (DMC) will not be established. The principal investigator (PI) is responsible for the ongoing monitoring of trial safety and quality, assisted by an independent clinician not involved in trial execution or outcome assessment. When approximately 50% of participants have completed the intervention, the PI will conduct a formal review of safety data, summarizing and analyzing all reported adverse events. The PI retains the ultimate decision-making authority regarding trial continuation. Due to the difficulty of obtaining statistically significant interim results in the early stages, this study will not incorporate any formal interim analyses or pre-specified stopping rules based on efficacy.

### Sample size

2.8

The primary outcome of this study is the NSSI level score of participants. Let n_1_ and n_2_ respectively represent the sample sizes of the intervention group and the control group. The study sets α = 0.05, β = 0.20 (two-sided test), with a statistical power (1-β) of 80%. The sample size ratio between the two groups is n_1_:n_2_ = 1:1. A previous RCT conducted in Chinese adolescents with comorbid MDD and NSSI, the same target population as this study, was referenced; the primary outcome in that trial was also assessed using the ASHS (40). The mean difference between the intervention and control groups was μ_1_ - μ_2_ = 13, with a standard deviation σ = 17.59. Substituting these values into the formula yielded n_1_ = n_2_ ≈ 29. Accounting for an estimated 10% attrition rate, the final calculated sample size is 33 participants per group, resulting in a total of 66 participants for the study.

$$n=\frac{2\;{\left(Z_{1-\alpha /2}+Z_{1-\beta }\right)}^{2}\;\sigma^{2}}{{\left(\mu_{1}-\mu_{2}\right)}^{2}}$$

### Statistical methods

2.9

Statistical analysis will be conducted by an independent statistician blinded to group allocation using SPSS 26.0 software. The analysis will adhere to the intention-to-treat (ITT) principle, employ two-sided tests, and consider a P-value of less than 0.05 as statistically significant.

The analysis of outcome measures will utilize three datasets: the full analysis set (FAS), the per-protocol set (PPS), and the safety set (SS). The FAS includes all randomized participants, analyzed according to their originally assigned groups. This is the primary dataset for efficacy analysis. All randomized participants are analyzed in the groups to which they were initially allocated. For missing data in the FAS, the primary outcome will be handled using multiple imputation to generate a complete dataset, upon which the primary analysis will be based. To assess the robustness of the results, a sensitivity analysis will be performed using the last observation carried forward (LOCF) method for imputation. The PPS includes participants with good adherence, who completed the full intervention, and had no major protocol deviations. This set will serve as another sensitivity analysis dataset to verify the stability of the primary analysis results. The SS includes all participants who received at least one dose of the intervention and is used for safety analyses. The evaluation of intervention effects for primary and secondary outcomes will primarily draw conclusions based on the analysis of the multiply-imputed FAS. The results from the LOCF-imputed FAS analysis and the PPS analysis will serve as sensitivity analyses to support the robustness of the conclusions. Safety indicators, such as the incidence of allergic reactions and adverse events, will be analyzed within the SS.

This study will conduct sensitivity analyses to evaluate the robustness of the results. These analyses will include repeating the primary analysis based on the FAS with missing data imputed using the LOCF method, as well as repeating the primary analysis on the PPS. If any baseline variables show imbalance (*P* < 0.1), they will be included as additional covariates in the model, followed by a corresponding sensitivity analysis.

Prior to the intervention, baseline characteristics and baseline outcome measures will be compared between the two groups to assess the balance achieved by randomization. Normally distributed continuous variables will be presented as mean ± standard deviation (SD) and compared using the independent samples t-tests. Non-normally distributed continuous variables will be presented as median and interquartile range (Median, IQR) and compared using the Mann-Whitney U test. Categorical variables will be presented as frequency and percentage (n, %) and analyzed using Chi-square test or Fisher’s exact test.

Analysis of Covariance (ANCOVA) will be used to assess the intervention effects. The post-intervention (T_1_) score will serve as the dependent variable, with the group assignment as a fixed factor and the corresponding baseline (T_0_) score included as a covariate in the model. Analysis of Covariance (ANCOVA) will be used to assess the intervention effects. The post-intervention (T_1_) score will serve as the dependent variable, with the group assignment as a fixed factor and the corresponding baseline (T_0_) score included as a covariate in the model. The primary outcome is a single endpoint and is exempt from multiplicity adjustment. To control for inflation of Type I error due to multiple comparisons across the five secondary outcomes, the Benjamini-Hochberg False Discovery Rate (FDR) correction will be applied to the following outcomes as a family: depressive symptoms measured by HAMD-17, alexithymia measured by TAS-20, self-efficacy measured by GSES, sleep quality measured by PSQI, and loneliness measured by UCLA-LS. A Generalized Linear Mixed Model (GLMM) will be used for a secondary analysis of the primary outcome. A Generalized Linear Mixed Model (GLMM) will be used for a secondary analysis of the primary outcome.

A reduction of ≥30% in the NSSI level score from baseline is prespecified as the minimal clinically important difference (MCID). Participants who achieve this reduction are defined as responders, and the responder rate will be compared between groups using the chi-square test or Fisher’s exact test. For all outcomes, effect sizes (Cohen’s d) with 95% confidence intervals will be reported.

To account for potential confounding arising from heterogeneity in TAU, the following variables derived from the systematically recorded TAU components will be prespecified as covariates and entered simultaneously into the primary ANCOVA model: number of psychotherapy sessions received as a continuous variable, antidepressant dose as a continuous variable, and receipt of physical therapy, defined as rTMS or ECT and coded as a binary variable. Rehabilitation training will be examined descriptively by group; if a between-group difference at *P* < 0.10 is detected, this variable will be added as an additional covariate in sensitivity analyses. When repeating the primary analysis on the LOCF-imputed FAS and the PPS, all prespecified TAU covariates will be retained in the model to verify the robustness of the adjusted treatment effect.

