### Study design

2.1

This is a single-center, block-randomized, two-arm parallel randomized controlled trial (RCT). The study protocol adheres to the SPIRIT 2025 statement (27). Participants are allocated in a 1:1 ratio to two groups via block randomization. The control group receives treatment as usual (TAU). The intervention group will receive Therapeutic Hrticulture (TH) in addition to TAU. The intervention period is two weeks. Assessments are conducted at baseline (T_0_) and immediately post-intervention (T_1_). The study flowchart is presented in **Figure 1**, and the schedule of enrollment, interventions, and assessments is detailed in **Table 1**.

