This study also has several limitations. First, outcomes were assessed only at baseline and immediately post-intervention. Without follow-up data, whether the effects of TH persist beyond the intervention period remains unknown. Future studies should include at least one follow-up assessment, such as 4 to 12 weeks post-intervention. Second, this single-center trial was conducted in an inpatient psychiatric ward, which, while ensuring standardized intervention delivery, limits generalizability to outpatient and community settings where most adolescents with MDD and NSSI receive care. Third, the sample was restricted to Chinese adolescents, and the findings may not extend to other populations. Fourth, the sample size is powered primarily to detect a moderate-to-large effect; smaller but potentially clinically meaningful effects may not be detected. A future multi-center pragmatic trial incorporating outpatient and community settings, a more diverse sample, and longer-term follow-up is warranted to evaluate the effectiveness of TH in real-world clinical contexts.

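### With only T0 and T1, the LOCF sensitivity analysis is baseline carried forward: one fixed no-change assumption, not reliably conservative, and a weak test of the multiple imputation

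*Protocol article*

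**What the plan says.** In the Statistical methods section, the full analysis set is the main efficacy set, and "the primary outcome will be handled using multiple imputation to generate a complete dataset, upon which the primary analysis will be based". To check robustness, "a sensitivity analysis will be performed using the last observation carried forward (LOCF) method for imputation". Data collection and quality control repeats this pairing, and the paragraph on treatment-as-usual covariates keeps those covariates in the LOCF repeat. The other robustness check is the per-protocol set: "The PPS includes participants with good adherence, who completed the full intervention, and had no major protocol deviations". The LOCF and per-protocol results are both meant to support the conclusions.

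The analysis model is ANCOVA: "The post-intervention (T_1_) score will serve as the dependent variable, with the group assignment as a fixed factor", with the T0 score as covariate.

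Study design, the schedule table and Data collection and quality control show two assessments and none in between. The limitations paragraph of the Discussion confirms that "outcomes were assessed only at baseline and immediately post-intervention".

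For participants who stop the intervention early, "every effort will be made to collect all primary and secondary outcome measures at the originally scheduled time point". The discontinuation criteria allow withdrawal for significant clinical deterioration. The Safety section withdraws participants after a serious adverse event, a category that includes clinically significant worsening of severe self-injurious behavior.

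**The concern.** LOCF presupposes at least one post-baseline value to carry forward. Here there is none, so a participant without T1 receives the T0 score and counts as unchanged. Both arms receive active inpatient treatment and may well improve. LOCF therefore sets dropouts in each arm back by whatever that arm gained, and its result depends on how many each arm loses and how much the ward improves overall.

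The question a robustness check should answer is different: how much worse would the unseen T1 scores have to be, particularly in the TH arm, before the conclusion changed? It is a real question here, because withdrawal can follow worsening in the very domain that the primary outcome measures. A participant withdrawn because self-injury worsened, with no T1, would be scored by LOCF as unchanged. If LOCF agrees with the primary result, the report could claim more robustness than was tested. If it disagrees, the cause could be dropout imbalance alone.

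**Working it through.** **Inputs from the article (Sample size section).** Effect 13, SD 17.59, two-sided alpha 0.05, power 80%, attrition 10%, 33 per arm.

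**Reproducing the plan's figure.** 2 × (1.960 + 0.842)² × 17.59² / 13² = 28.74, rounded up to 29 per arm. 29 / 0.9 = 32.2, rounded up to 33, or 66 in total. This agrees with the article. Ten percent of 33 is 3.3, so about 3 to 4 participants per arm would lack T1.

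**Assumptions, not in the article.** Control-arm mean improvement D of 0, 10 or 20 points; dropout splits of 10%/10% and 15%/5% in either direction; missingness unrelated to outcome in the first three steps. Benefit of TH is written as positive.

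**Step 1: what LOCF estimates.** Let pT and pC be the proportions missing T1 in the TH and control arms. Completers improve by D + 13 and D, and dropouts by 0:

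LOCF effect = (1 − pT)(D + 13) − (1 − pC)D

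| Dropout TH / control | D = 0 | D = 10 | D = 20 |
|---|---|---|---|
| 10% / 10% | 11.70 | 11.70 | 11.70 |
| 15% / 5% | 11.05 | 10.05 | 9.05 |
| 5% / 15% | 12.35 | 13.35 | 14.35 |

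For example, 0.85 × 33 − 0.95 × 20 = 28.05 − 19.00 = 9.05, and 0.95 × 33 − 0.85 × 20 = 31.35 − 17.00 = 14.35. Under these conditions a missing-at-random analysis recovers 13 throughout. Large-sample ANCOVA simulations (T0–T1 correlation 0.5 assumed, treatment-as-usual covariates left out) gave LOCF estimates from about 9.0 to 14.4, in agreement with the table.

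**Step 2: when LOCF favors TH.** It exceeds 13 when pC × D > pT × (D + 13). At 5% TH / 15% control this is 0.15D > 0.05D + 0.65, so D > 6.5 points.

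**Step 3: no true effect.** The LOCF difference is (pC − pT) × D. At D = 20 with a 15%/5% split it is 0.10 × 20 = 2 points, for or against TH. At D = 0 it is 0.

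**Step 4: response to how dropouts fared.** Take 10% dropout in both arms and make the unseen T1 scores of TH dropouts worse than a missing-at-random model predicts:

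| Worsening of unseen TH scores | True effect | Missing-at-random estimate | LOCF |
|---|---|---|---|
| 0 | 13.0 | 13.0 | 11.7 |
| 13 | 13 − 0.10 × 13 = 11.7 | 13.0 | 11.7 |
| 26 | 13 − 0.10 × 26 = 10.4 | 13.0 | 11.7 |

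The truth moves and LOCF does not. The two coincide only in the middle row.

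**Step 5: what LOCF assumes.** At D = 20, missing-at-random imputation credits TH dropouts with an improvement of about 33 and control dropouts with 20. LOCF removes both, which amounts to worsening TH dropouts by 33 (33 / 17.59 = 1.9 SD) and control dropouts by 20. At 10%/10% the net loss is 0.10 × 33 − 0.10 × 20 = 1.3, the gap between 13 and 11.7.

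**The case against.** Several points on the other side have force.

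- **LOCF is itself a departure from missing at random.** A reader might infer that it says nothing about data missing not at random, or never considers TH dropouts doing worse than imputed. Step 5 shows otherwise: when patients improve, LOCF penalizes TH dropouts, at D = 20 by more than 1 SD. What stands is that this is a single ungraded scenario, it penalizes control dropouts too, and its net direction depends on dropout balance.
- **Standard error.** A reader might infer that single imputation must make the LOCF standard error too small. LOCF does treat filled-in values as observed, but simulation of this ANCOVA at 33 per arm and 10%/10% dropout does not support the inference. With random dropout counts, model and empirical standard errors were close: 3.68 against 3.65 at D = 0, and 4.15 against 4.23 at D = 20. With the number of dropouts held fixed at D = 20, the model value was the larger (4.14 against 3.67).
- **Size.** The 20-point improvement and the unequal splits are assumptions. With no true effect and unequal dropout, the simulated rejection rate was 4.5% to 5.8% with fixed dropout counts. It reached about 8% at D = 20 when counts varied at random. A 15%/5% split of 33 is only about 5 against 2 participants.
- **Role.** Conclusions rest on the multiply imputed analysis. The trial lasts two weeks in a closed ward, and T1 is sought from those who stop the intervention early. That limits the missing data but does not remove it, and the article does not make clear whether the effort extends to participants withdrawn from the study itself.
- **Further detail elsewhere.** The list of sensitivity analyses is not worded as exhaustive, and a fuller analysis plan could add more. The point is therefore not the absence of a tipping-point analysis. It is that the article fixes LOCF as the missing-data check. The per-protocol repeat does not replace such a check, because it restricts the sample to adherent completers and varies no assumption about unseen scores.

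**Conclusion.** The concern holds in a limited form. That LOCF here equals baseline carried forward follows from the two-visit design and needs no assumption. That it is not reliably conservative follows from the arithmetic: for a true effect of 13 it ranges from about 9.1 to 14.4 over the assumed conditions, and with no true effect unequal dropout shifts it by 0 to 2 points either way. These figures rest on the assumed control improvement and dropout splits. Missing at random is inferred as the usual basis of multiple imputation.

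Nothing here shows that the primary estimate is biased or that 66 participants are too few, and neither should be inferred. The consequence is that agreement between LOCF and the primary analysis would be weak evidence of robustness. With about 3 to 4 participants per arm affected, this is an inexpensive improvement of modest impact.

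**What to change.** Keep multiple imputation as the primary method and state the assumption on which it rests. Replace LOCF, or at least supplement it, with delta-adjusted multiple imputation:

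- use the same imputation model and the same ANCOVA covariates as the primary analysis;
- worsen the imputed T1 scores in the TH arm in steps, for example 0, 0.25, 0.5 and 1 SD (0, 4.4, 8.8 and 17.6 points at SD 17.59);
- pool each step by Rubin's rules;
- extend the steps until the conclusion changes, and report that tipping point with the number of participants imputed per arm.

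Extension may well be needed: with 10% missing in the TH arm, a 1 SD shift moves the estimate by only 0.10 × 17.59 = 1.8 points. If LOCF is kept, call it baseline carried forward and do not describe it as conservative.

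The wording should be settled before unblinding. The cost is a text change and a few more analysis runs, with no new data, visits or participants. The figures 29, 33 and 66 stay as they are.

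### The responder comparison uses an unadjusted chi-square or Fisher test that yields no effect estimate and, for Fisher, does not fit the multiple-imputation plan; baseline-adjusted logistic regression would serve better

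*Protocol article*

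**What the plan says.** All of this stands in section 2.9, Statistical methods.

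- **Definition.** A fall of at least 30% from the participant's own baseline NSSI level score is set as the minimal clinically important difference. "Participants who achieve this reduction are defined as responders".
- **Test.** "the responder rate will be compared between groups using the chi-square test or Fisher’s exact test". No covariate is named.
- **Effect measure.** "For all outcomes, effect sizes (Cohen’s d) with 95% confidence intervals will be reported". No risk difference, risk ratio or odds ratio is named.
- **Analysis of the same score as a continuous outcome.** ANCOVA of the T1 score on group, with "the corresponding baseline (T_0_) score included as a covariate in the model".
- **Missing data.** In the full analysis set (FAS), "the primary outcome will be handled using multiple imputation to generate a complete dataset". The evaluation of primary and secondary outcomes "will primarily draw conclusions based on the analysis of the multiply-imputed FAS".

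The Sample size section (2.8) concerns the continuous score only. It states no responder rates and no power for the responder comparison.

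**The concern.** This is the only analysis in the article that applies the prespecified clinically important difference, so it is where a clinician will look for the size of the benefit. Three features fit the rest of the plan badly.

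1. **No estimate.** Chi-square and Fisher tests return a p-value. Cohen's d is a standardised difference of means and does not describe a difference between two proportions.
2. **Imputation.** Responder status is computed from the T1 score, which is multiply imputed where missing, so it can differ from one imputed data set to the next. Rubin's rules need an estimate and a standard error from each data set. Fisher's test supplies neither.
3. **Baseline left out of the test.** Baseline enters through the percent-change definition, but the chance of meeting a percent-change rule can still depend on the starting value through regression to the mean. The ANCOVA allows for that and the responder test does not.

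At stake are a result that is hard to interpret and some possible loss of power. Bias is not at stake.

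**Working it through.** **Numbers per arm.** The Sample size section gives a difference of 13, SD 17.59, two-sided α = 0.05 and 80% power:

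n = 2(1.96 + 0.84)² × 17.59² / 13² = 28.74, rounded up to 29. With 10% attrition, 29 / 0.9 = 32.2, rounded up to 33.

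Both stated figures reproduce, so the responder test will have about 29 to 33 per arm.

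**Can the named tests be pooled?** One illustrative data set was used: 33 per arm, assumed responder rates 30% and 60%, about 10% missing, m = 20 imputations.

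- Chi-square, D2 rule: D2 = [w̄ − ((m+1)/(m−1)) r] / (1 + r), where w̄ is the mean chi-square statistic and r = (1 + 1/m) × Var(√w). With w̄ = 3.83 this gives F = 3.61, p = 0.057.
- Risk difference, Rubin's rules: total variance T = W̄ + (1 + 1/m)B, the within- and between-imputation parts. Result 0.239, 95% CI −0.000 to 0.479.
- Fisher: a p-value only, with no standard pooling rule.

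**What an interval adds.** Chi-square power at assumed rates of 30% v 60% is 70% with 33 per arm and 64% with 29. At 30% v 50% it is 38% and 34%. A bare p-value will therefore often say little. With observed rates of 30% and 60% and 33 per arm, the half-width of the 95% CI is 1.96 × √(0.6×0.4/33 + 0.3×0.7/33) = 0.23, so the risk difference would read 0.30 (0.07 to 0.53).

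**When does baseline predict response?** Let ρ be the baseline–T1 correlation and assume equal SDs at both times.

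- Lognormal score: response means log T1 ≤ log T0 + log 0.7. The probit slope per SD of log baseline is (1 − ρ)/√(1 − ρ²) = 0.73, 0.58 and 0.42 at ρ = 0.3, 0.5 and 0.7.
- Normal score: response means T1 ≤ 0.7 × T0. Ignoring the floor at zero, the slope per SD is (0.7 − ρ)/√(1 − ρ²) = 0.42, 0.23 and 0.

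So how much adjustment can gain depends on the shape of the score and on ρ, and the article gives neither.

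**Simulated power (%), in the order ρ = 0.3 / 0.5 / 0.7**

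| Assumed score, n per arm | Chi-square | Fisher | Logistic with baseline | Gain over chi-square (points) |
|---|---|---|---|---|
| Lognormal, 29 | 46.8 / 59.9 / 78.1 | 36.2 / 49.0 / 69.6 | 58.4 / 67.0 / 82.9 | +11.6 / +7.1 / +4.8 |
| Lognormal, 29, Wald test, separate runs | 47.2 / 61.0 / 82.2 | not run | 55.6 / 67.6 / 84.2 | +8.4 / +6.6 / +2.0 |
| Normal, mean 40, 33 | 66.7 / 78.9 / 92.1 | 57.3 / 71.1 / 88.1 | 67.5 / 77.5 / 90.9 | +0.8 / −1.4 / −1.2 |
| Normal, mean 60, 33 | 63.3 / 74.9 / 88.2 | 52.7 / 64.3 / 81.6 | 67.3 / 76.3 / 88.1 | +4.0 / +1.4 / −0.1 |
| Normal, mean 50, 29, Wald test | 58.0 / 69.2 / 86.0 | not run | 61.6 / 70.8 / 86.0 | +3.6 / +1.6 / 0.0 |

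Lognormal: log T0 ~ N(3.2, 0.6²), log T1 ~ N(2.9 − 0.45 × group, 0.6²), which gives responder rates of about 46% v 70–80%. Normal: the article's difference of 13 and SD 17.59, with an assumed control improvement of 5 points. There were 800 to 2,000 trials per setting. The normal rows at means 40 and 60 use a likelihood-ratio test, which also reproduces the +11 to +12 points in the first row. The Wald test is the closer match to a coefficient pooled by Rubin's rules. Further Wald runs gave about +2 to +9 points (lognormal), −2 to +8 (gamma) and −2 to +3 (normal, SD 17.59).

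Under no effect, chi-square rejected in about 5–7% of trials, adjusted logistic in about 4–8% (Wald 4–6%) and Fisher in about 2–3.5%.

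**The case against.** The case for leaving the text alone is substantial.

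- **Validity.** Comparing randomised arms without covariates is valid, and the simulations show no bias. This stands. It would also be wrong to say that the analysis ignores baseline altogether, because baseline is built into the definition of response.
- **Pooling.** A reader might infer that the responder analysis cannot be run on the imputed data, or that the single complete data set in the imputation sentence means one imputed set will be used. The documents support neither. Chi-square pools by D2, a risk difference pools by Rubin's rules, and the same sentence specifies multiple imputation. At responder rates of 46% and 80% with 29 per arm, the smallest expected count is 29 × (0.54 + 0.20)/2 = 10.7, so chi-square would be the usual choice. The pooling gap is confined to Fisher.
- **Level of detail.** How a supportive test is combined over imputations can be left to a fuller analysis plan. That is fair, so the missing pooling rule is not a fault in itself. The point is that the article fixes a test and an effect measure that do not suit a binary result from imputed data.
- **Power.** A reader might infer a clear loss of power. With the article's own difference and SD and a normal score, the gain is close to zero. A skewed score is plausible, since the level is a product of frequency and harm, but its distribution is not given. Much of the gap to Fisher is Fisher's conservatism rather than the missing covariate.
- **Estimate.** Comparing responder rates implies that percentages by arm will be shown. That softens the point, but percentages alone carry no confidence interval for the difference.

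**Conclusion.** The point holds as a minor improvement. For its only comparison based on the clinically important difference, the plan names a test without an estimate and promises an effect measure that does not fit. One of the two tests it names has no standard pooling rule under its own imputation scheme. A better method is available from data already collected.

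The argument does not rest on power. Against chi-square, baseline adjustment is worth roughly −2 to +12 points at 29 to 33 per arm. The upper end needs a skewed score, a baseline–T1 correlation near 0.3 and a likelihood-ratio test. For a normal score with SD 17.59 the gain is near zero. The score distributions, baseline means, correlations and control improvement are all assumptions.

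The responder comparison is supportive. It lies outside the sample-size calculation and outside the family of five secondary outcomes with false-discovery-rate control. The primary ANCOVA conclusion and the 66 participants are unaffected.

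**What to change.** Replace the test sentence in Statistical methods with the following steps.

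1. Derive responder status from the T0 and T1 scores within each imputed data set.
2. In each data set, fit a logistic regression of response on group and baseline NSSI level score.
3. Pool by Rubin's rules. Report the odds ratio and a standardised (marginal) risk difference, each with a 95% CI.
4. Keep the raw responder percentages by arm as description, and limit Cohen's d to the continuous scores.

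The cost is a few lines of wording and code, with no new data. The standardised risk difference may need a short script outside the named SPSS package; the trial already uses R for its randomisation sequence. There are two downsides. The odds ratio is conditional on baseline, which is why the risk difference should accompany it. A penalised fit should be named in advance in case cells are sparse, for instance if nearly everyone in one arm responds.
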